## Discussion

To the best of our knowledge, the OPTIMA study will be the first study to evaluate tumor molecular profiling, *UGT1A1* genotype and GUS activity as potential biomarkers for efficacy and toxicity of irinotecan-based systemic treatment in patients with advanced CRC. By combining these three biomarkers into one study, we will provide pivotal new insights for clinicians to make well-considered choices concerning for instance the initiation, dose adjustments or the need for microbiota modulation during irinotecan-based systemic treatment in this patient population.

The tumor molecular profiling will provide new insights into which patients are expected to benefit from irinotecan-based systemic treatment. As outlined in the introduction, irinotecan-based systemic treatment is probably not the optimal choice in all CMS subtypes. Validation of these previous findings in the current cohort will significantly strengthen the rationale for a more personalized treatment selection based on the tumor molecular profile.

Furthermore, OPTIMA will further evaluate the use of *UGT1A1* genotype and subsequent dose adjustments in clinical practice. If a 70% dose intensity in UGT1A1 PMs leads to similar incidences of severe toxicity as compared to UGT1A1 NMs and IMs treated with the full dose, this further supports the validity and utility of this biomarker.

In addition, new knowledge on the role of bacterial GUS in a clinical setting, will enhance the detection of patients who are expected to experience high GI toxicity before start of the treatment. This opens the opportunity to modulate GUS activity in these patients by targeted gut microbiota modulation.

However, there are some limitations inherent to the current study. Due to the inclusion of patients receiving different treatment regimens, as well as potential treatment delays in individual patients, the time between two consecutive sampling time points might differ between patients. Additionally, we only ask patients to report overall dietary patterns and do not collect detailed data on dietary intake, which might influence particularly the gut microbiota parameters. Lastly, due to the advanced setting, patients might have distinct and complex medical histories, co-morbidities and co-medication which could influence the outcomes.

On the other hand, the unique strengths of the OPTIMA study are the multidisciplinary and multi-center character, the combination of three different biomarkers as well as the longitudinal design with repeated sampling per patient. In addition, we include baseline sampling before treatment initiation, which enables us to investigate treatment-related effects. The comprehensive collection of biological specimens as well as clinical data is a further advantage of the current study.

To conclude, results obtained in the context of the OPTIMA study will greatly contribute to the optimization of efficacy and the reduction of toxicity of irinotecan-based systemic treatment, thereby significantly improving QoL of patients. In view of the fact, that the maintenance of QoL is of particular relevance in the palliative setting, the OPTIMA study will be of great benefit for patients as well as their caregivers.

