## Background

Colorectal cancer (CRC) represents a major public health concern as it is the third most frequently diagnosed cancer and the second cause of cancer-related mortality worldwide [1]. In 2022, 21% of patients with newly diagnosed CRC in the Netherlands suffered from metastatic disease [2]. In this group of patients, irinotecan-based systemic treatments are commonly applied to relieve symptoms, improve quality of life (QoL) and extend overall survival (OS).

However, the individual response to irinotecan-based treatment differs consistently between patients, and is currently largely unpredictable. Previous research indicated that molecular tumor characteristics might be associated with response to irinotecan-based systemic treatment. CRC can be subdivided into four consensus molecular subtypes (CMS1-4), based on different gene expression profiles [3]. Ten Hoorn et al. concluded based on a meta-analysis that specifically in CMS4 metastatic disease, patients benefit more from irinotecan-based regimens compared with oxaliplatin-containing regimens [4].

An additional disadvantage of irinotecan-based systemic treatment is the occurrence of systemic (primarily neutropenia) and late-onset gastrointestinal (GI) toxicity, (primarily diarrhea). For instance, grade 3–4 neutropenia has been previously identified in 46% and grade 3–4 diarrhea in approximately 18% of patients [5, 6]. The occurrence of severe toxicity often leads to irinotecan dose reduction, or premature discontinuation of the treatment. This negatively affects not only the patient’s QoL and OS, but also puts significant pressure on family and caregivers, as well as on hospitalization-related healthcare costs [7]. Consequently, there is an urgent need for biomarkers to identify patients at risk for developing irinotecan-induced toxicity. In this context, two promising candidate biomarkers are 1) the UDP Glucuronosyltransferase Family 1 Member A1 (*UGT1A1*) genotype of the patient and 2) the microbial enzyme β-glucuronidase (GUS).

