## Methods and study design

### Aims of the study

The primary objectives of this study are:To investigate whether tumor molecular markers can predict the response to irinotecan-based systemic treatment and are associated with QoL and OS;To validate the safety of *UGT1A1* genotype-guided dose adaptation (70% dose intensity) in UGT1A1 PMs;To assess whether high bacterial GUS enzyme activity is associated with irinotecan-induced GI toxicity, decreased QoL and OS

The most important secondary objectives of this study are:To investigate the dynamics in GUS activity and overall gut microbiota composition, diversity and functional capacity during irinotecan-based systemic treatment;To assess associations between GUS activity and gut microbiota composition, diversity and functional capacity,To measure fecal levels of SN-38 and SN-38-G and to determine its association with gut microbiota composition, bacterial GUS activity, *UGT1A1* genotype, treatment response and toxicity;To correlate tumor molecular profile, GUS activity and other clinical characteristics (e.g. physical performance and nutritional status) during irinotecan-based systemic treatment.

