### Study design

OPTIMA is a prospective, observational, multi-center cohort study conducted at the Maastricht University Medical Centre + (MUMC +, Maastricht), Catharina Hospital (Eindhoven), VieCuri Medical Center (Venlo), Amsterdam University Medical Center (AUMC, Amsterdam), Van Weel-Bethesda Hospital (Dirksland), Hospital Gelderse Vallei (Ede) and Rode Kruis Hospital (Beverwijk), all situated in the Netherlands. The study will be conducted according to the guidelines of the Declaration of Helsinki and Good Clinical Practice and is approved by the Medical Ethics Committee of azM/UM (METC 2022–3247)and the Institutional Review Board of MUMC + (RvB/301756/ReWi). This study has been registered in the ClinicalTrials.gov register (NCT05655780). All patients will sign written informed consent prior to enrollment.

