#### Study population

Patients will be included via the oncologic outpatient clinics of the participating centers. Patients are eligible if they are ≥ 18 years of age, diagnosed with advanced CRC, and planned to start with irinotecan-based systemic treatment, if applicable in combination with anti-EGFR treatment. Additionally, patients must have a WHO performance status 0–2, minimal acceptable safety laboratory values at baseline, defined as: ANC of ≥ 1.5 × 109/L, platelet count of ≥ 100 × 109/L, serum bilirubin ≤ 1.5 × ULN, ALAT and ASAT ≤ 2.5 × ULN; in case of liver metastases ALAT and ASAT ≤ 5 × ULN, and renal function (eGFR) ≥ 50 ml/min or creatinine ≤ 1.5 × ULN.

Exclusion criteria are: microsatellite instability (MSI) or deficient MMR proteins, being pregnant or nursing, presence of an ileostomy, Asian ethnicity, other systemic treatment within < 1 month before inclusion, therapeutic antibiotic use within < 3 months before inclusion, abdominal radiotherapy within < 2 weeks before inclusion, being physically or mentally incapable or incompetent, more than 25% irinotecan dose reduction at the start of treatment (dose reductions during treatment are allowed), with exception of dose reduction in UGT1A1 PMs.

Patients can be treated with combination chemotherapy (FOLFOXIRI/FOLFIRI) or irinotecan monotherapy and will follow the regular treatment regimens, according to the Dutch guidelines (Table 1).

**Table 1 Tab1:** Overview of irinotecan-based treatment regimens

		**Compounds**	**Number of weeks per cycle**	**Possible addition of bevacizumab?**	**Possible addition of anti-EGFR?**
Treatment	FOLFOXIRI	Irinotecan 5-FU Folinic acid Oxaliplatin	2	yes	no
	FOLFIRI	Irinotecan 5-FU Folinic acid	2	yes	yes
	Monotherapy	Irinotecan	3	no	no

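### The Discussion promises to validate a CMS4 irinotecan-versus-oxaliplatin finding and show who benefits from irinotecan, but a cohort in which every regimen contains irinotecan cannot estimate either

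*Protocol article*

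**What the plan says.** The Background of the protocol article cites a meta-analysis which concluded that "specifically in CMS4 metastatic disease, patients benefit more from irinotecan-based regimens compared with oxaliplatin-containing regimens".

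On the design, "OPTIMA is a prospective, observational, multi-center cohort study". Under Study population, eligible patients are those "planned to start with irinotecan-based systemic treatment, if applicable in combination with anti-EGFR treatment". The same section states: "Patients can be treated with combination chemotherapy (FOLFOXIRI/FOLFIRI) or irinotecan monotherapy and will follow the regular treatment regimens". Table 1 lists irinotecan among the compounds of all three regimens; oxaliplatin appears only in FOLFOXIRI, together with irinotecan.

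The first primary objective is "To investigate whether tumor molecular markers can predict the response to irinotecan-based systemic treatment and are associated with QoL and OS". For the CMS part, the section on analysis of the main outcome parameters plans chi-squared tests of CMS subtype against RECIST category and Kaplan-Meier curves by subtype. It names no comparator for this objective. Historical controls are named only for toxicity in UGT1A1 poor metabolizers.

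The Discussion then says: "The tumor molecular profiling will provide new insights into which patients are expected to benefit from irinotecan-based systemic treatment". It refers back to the introduction for the view that irinotecan may not suit every CMS subtype equally well, and continues: "Validation of these previous findings in the current cohort will significantly strengthen the rationale for a more personalized treatment selection". The limitations paragraph covers sampling intervals, dietary data and medical history. It does not mention the absence of a comparator.

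**The concern.** Benefit from a treatment, and the choice between treatments, are comparative quantities. The Discussion claims both, and claims to validate an earlier comparative result, from patients who all receive the same key drug. A difference in response or survival between CMS subtypes in this cohort could arise because the subtypes differ in prognosis whatever the chemotherapy, because irinotecan works differently in them, or both.

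At stake is the conclusion attached to a primary objective. If a subtype difference under irinotecan is read as a difference in benefit from irinotecan, a subtype could be judged suitable or unsuitable for the drug on evidence that fixes neither the size nor the sign of its differential benefit.

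**Working it through.** The document gives no effect size, power or target precision for the CMS objective, so there is no figure of the plan to reproduce. The check concerns what the design can estimate.

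**Step 1: what the cited meta-analysis result requires.** Write R for the response rate by treatment (irinotecan or comparator) and subtype (CMS4 or other).

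- Benefit within CMS4 = R(irinotecan, CMS4) − R(comparator, CMS4).
- Differential benefit = [R(irinotecan, CMS4) − R(comparator, CMS4)] − [R(irinotecan, other) − R(comparator, other)].

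Rearranged, differential benefit = D − C, where D is the CMS4-minus-other difference under irinotecan and C is the same difference under the comparator.

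**Step 2: what OPTIMA supplies.** By eligibility and Table 1 every planned regimen contains irinotecan. The cohort yields the two irinotecan terms, hence D. It yields neither comparator term, so C is unobserved, and so is the benefit within CMS4.

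**Step 3: whether oxaliplatin within FOLFOXIRI helps.** A contrast of FOLFOXIRI with FOLFIRI would ask what adding oxaliplatin to irinotecan does, which is a different question from irinotecan versus oxaliplatin. It would also be non-randomised, is not planned by CMS, and would involve regimens with different permitted partners (Table 1 allows anti-EGFR with FOLFIRI but not with FOLFOXIRI).

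**Step 4: size of the ambiguity.** The rates here are assumptions for illustration; none comes from the document. Fix the irinotecan rates at 55% (CMS4) and 40% (other), so D = 55 − 40 = +15 points in every row.

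| Assumed comparator rates, CMS4 / other | C | Differential benefit D − C | Meaning |
|---|---|---|---|
| 40% / 25% | +15 | 15 − 15 = 0 | purely prognostic |
| 30% / 40% | −10 | 15 − (−10) = +25 | irinotecan favoured more in CMS4 |
| 60% / 25% | +35 | 15 − 35 = −20 | irinotecan favoured less in CMS4 |

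In the third row the benefit within CMS4 is itself negative: 55 − 60 = −5 points.

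Without any assumption on the comparator, C can lie anywhere from −100 to +100 points, so D − C is bounded only between 15 − 100 = −85 and 15 + 100 = +115 points. A larger cohort would estimate D more precisely and leave C just as unknown.

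**The case against.** The strongest reply is that the operative parts of the plan are sound. Objective 1 asks whether markers can forecast response and whether they are associated with QoL and OS. The Methods part of the abstract and the analysis section both speak of association. No treatment-by-CMS interaction and no rule for choosing treatment by CMS is planned. **This stands.** A reader might infer that Objective 1 itself claims to predict irinotecan benefit. Its text does not support that: forecasting outcome among irinotecan-treated patients is a question that this cohort can address.

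A second reply is that the plural reference to earlier findings is loose. The Background also mentions a possible association of tumor characteristics with response to irinotecan, which a single cohort can corroborate. This stands in part. However, the sentence just before concerns which CMS subtypes irinotecan suits and points back to the introduction, where the only CMS treatment result is the irinotecan-versus-oxaliplatin comparison. The sentence itself ends in treatment selection, which needs a comparison.

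A third reply is that the harm is hypothetical, since the document commits to no decision based on CMS. That is fair, and the rates above are only illustrative. The lack of identification does not depend on them.

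Nor is this a detail left to a fuller protocol or analysis plan. The document states an inference that its stated design cannot support, and no analysis plan can create an irinotecan-free group among these patients.

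**Conclusion.** The point holds for the Discussion. OPTIMA can estimate how CMS and mutational profile relate to response, QoL and OS under irinotecan-based treatment. It cannot confirm or refute the CMS4 irinotecan-versus-oxaliplatin contrast, and it cannot show which subtypes benefit from irinotecan. In the illustration one observed difference of +15 points fits a differential benefit of 0, +25 or −20 points.

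A reader might go further and infer that the cohort can show only a prognostic association. The documents do not support that label either. Without a comparator, prognostic and predictive effects cannot be told apart, so an observed CMS difference may be either or both.

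The conclusion rests on two readings: that the eligibility text and Table 1 describe all treatment in the cohort, and that no external comparator is intended for the CMS objective, none being named. Recruitment, data collection and the planned CMS tests are not affected by this point.

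**What to change.** - In the Discussion, replace the statements on validation, on who benefits and on treatment selection with: association of CMS and mutational profile with response, QoL and OS under irinotecan-based treatment.
- Add to the limitations that there is no irinotecan-free comparator and that differential benefit by CMS therefore cannot be inferred.
- Objective 1 needs at most a clarification that to predict means to forecast outcome among irinotecan-treated patients. It should not be relabelled as prognostic.

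The cost is wording only and a less ambitious claim. If the comparative claim is to be kept, it would need a suitable irinotecan-free comparison cohort and an analysis of the CMS-by-treatment interaction, which is a much larger undertaking.

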UGT1A1 is the main liver enzyme responsible for inactivation of SN-38 (the active metabolite of irinotecan) by conjugating it with glucuronic acid, resulting in SN-38G [8]. Certain *UGT1A1* polymorphisms (*UGT1A1*28* and *UGT1A1*93*) have been shown to be associated with reduced enzyme activity and an increased risk to develop neutropenia [8–10]. To prevent this toxicity, the clinical utility of *UGT1A1* genotyping with subsequent initial genotype-guided dose adaptation has been demonstrated [8]; however, is not yet routinely recommended in Dutch clinical guidelines [11].

The microbial enzyme GUS is expressed by certain gut bacteria [12]. GUS enzymes can remove glucuronic acid for microbial use as a carbon source, and in this way re-activate the inactive SN-38G into the cytotoxic SN-38 in the intestinal lumen [13]. This reactivation process has significant clinical implications, potentially resulting in severe mucosal damage and diarrhea [14]. Preclinical studies have demonstrated that the inhibition of GUS might be a promising method to limit SN-38-induced GI toxicity [15, 16]. However, this association has not been investigated in humans yet and requires further investigation. In addition, there are hundreds of different GUS enzyme variants found in human stool samples, with a broad diversity in structures, and functionality [12, 17, 18]. Therefore, it also remains to be established which specific microbes exert SN-38G-specific GUS activity and are related to irinotecan-induced GI toxicity in CRC patients.

In view of the studies described above, the tumor molecular profile, *UGT1A1* genotype and bacterial GUS are promising molecular markers for the prediction of irinotecan efficacy and toxicity. Therefore, the OPTIMA study aims to evaluate 1) whether tumor molecular profiling (e.g. CMS classification, transcriptomics) can predict the efficacy of irinotecan-based systemic treatment and is associated with QoL and OS, and 2) whether UGT1A1-guided dose reduction in UGT1A1 poor metabolizers (PMs) is safe to use, and 3) whether high GUS enzyme activity is associated with GI toxicity, decreased QoL and OS in patients with metastatic or unresectable CRC. These insights will greatly contribute to more personalized irinotecan-based treatment regimens as well as well-considered choices for other treatment options.

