#### UGT1A1 genotyping in blood samples and adaptation of irinotecan dose intensity

Before treatment initiation, the *UGT1A1* genotype of the patient will be assessed in blood using Polymerase Chain Reaction (PCR). Patients will be genotyped for *UGT1A1*28* (TA repeat; rs3064744; NC_000002.12:g.233760235TA[5_11]). DNA for genotyping will be isolated from 200µl of whole EDTA blood obtained prior to start of therapy. Genotyping will be conducted using validated real-time PCR reactions with appropriate wild type, heterozygous and homozygous controls in every run. Genotypes will be converted to phenotypes in the following manner: homozygous carriers of *UGT1A1*28* are defined as UGT1A1 PMs, heterozygous carriers are considered UGT1A1 intermediate metabolizers (IMs) and *UGT1A1* wild type individuals are considered UGT1A1 normal metabolizers (NMs). In UGT1A1 PMs the irinotecan starting dose will be reduced by 30% and further individualized in subsequent cycles of treatment based on ANC and clinical tolerance. The starting dose in UGT1A1 NMs and IMs will be left unchanged. Further dose modifications or treatment delays will be applied according to standard of care protocols and guidelines.

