#### Statistical and bioinformatic analysis of main outcome parameters

The association between CMS subtypes 1–4 and treatment response (categorized as progressive disease, stable disease, partial response and complete response) will be analyzed using chi-squared tests. Survival analysis within the different CMS subtypes will be done by Kaplan Meier curves.

To validate the safety of the 70% irinotecan starting dose intensity, toxicity in UGT1A1 PMs will be compared to historical control patients, i.e. cohorts of patients described in literature that are homozygous polymorphic for *UGT1A1*28* and were treated with full dose therapy. In addition, toxicity in UGT1A1 PMs will be compared to UGT1A1 non-PMs treated with full dose in the current study, under the assumption that these groups experience comparable degrees of toxicity.

Correlations between GUS activity and the degree of experienced late-onset GI toxicity during irinotecan-based treatment will be analyzed by means of the Spearman correlation coefficient. Furthermore, we will investigate whether GUS activity is different between patients without diarrhea vs. grade 1–2 diarrhea vs. grade 3–4 diarrhea by means of ANOVA or the Kruskal Wallis test, depending on whether the data are normally distributed or not. Longitudinal changes in GUS activity during irinotecan-based treatment will be analyzed using repeated-measures ANOVA or the Friedman test.

Bioinformatic analysis of the predicted GUS functionality derived from metagenomics sequencing will be conducted. A Hidden Markov Model (HMM)-profile will be made per orthologous group with predicted GUS functionality, based on a reference dataset of publicly available GUS protein sequences and the results of Pollet et al. [12, 26]. The HMM-profiles will be used to identify all predicted proteins with a potential GUS functionality per fecal sample. These predicted proteins will be used to create a non-redundant microbial GUS protein catalogue.

Changes in GUS activity and overall gut microbiota composition, diversity and potential GUS capacity during irinotecan-based systemic treatment will be assessed by redundancy analysis (RDA) [27] and ANOVA [28]. These data will be used to examine the microbial GUS variation and origin per fecal community in order to link the microbial composition and GUS functional potential to the measured GUS activity.

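### Similar severe toxicity in PMs at 70% dose and non-PMs at full dose cannot by itself support UGT1A1 validity: genotype and starting dose are confounded

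*Protocol article*

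**What the plan says.** All references are to the protocol article.

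- **Genotyping and dose section.** "In UGT1A1 PMs the irinotecan starting dose will be reduced by 30% and further individualized in subsequent cycles", whereas "The starting dose in UGT1A1 NMs and IMs will be left unchanged". For later cycles, "Further dose modifications or treatment delays will be applied according to standard of care protocols and guidelines".
- **Study population.** A reduction of more than 25% at the start excludes a patient, except for PMs. So no PM is planned to start at full dose, and no eligible non-PM can start at 70%.
- **Statistical analysis of the main outcome parameters.** Two comparisons are planned. In the first, "toxicity in UGT1A1 PMs will be compared to historical control patients", meaning published *28 homozygotes treated at full dose. In the second, "toxicity in UGT1A1 PMs will be compared to UGT1A1 non-PMs treated with full dose in the current study". This second comparison is made "under the assumption that these groups experience comparable degrees of toxicity".
- **Discussion.** The second comparison receives an interpretation: if the reduced dose "leads to similar incidences of severe toxicity as compared to UGT1A1 NMs and IMs treated with the full dose, this further supports the validity" of the biomarker, and its utility.
- **Background.** The *28 and *93 polymorphisms "have been shown to be associated with reduced enzyme activity and an increased risk to develop neutropenia", so the association is taken as prior knowledge.

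**The concern.** For UGT1A1 to be a valid toxicity biomarker, genotype has to change toxicity at a given dose. The internal comparison never observes that, because genotype and starting dose change together. A similar rate in the two groups can arise in two ways: genotype raises toxicity and the lower dose cancels it, or genotype does nothing and toxicity differs little between 70% and 100% dose. Later toxicity-driven dose changes, allowed in all groups, can also draw the rates together.

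The analysis section moreover starts from the assumption that the groups are comparable, and the Discussion then counts comparability as support. What is at stake is the wording of the conclusion on the second primary objective. A finding on tolerability of a dosing strategy could be reported as evidence on the biomarker itself.

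**Working it through.** **Plan's own figure.** None exists for this comparison. The 84 evaluable patients (22 + 62) were chosen for the precision of the GUS assay's sensitivity and specificity. I take 84 as given.

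**Inputs**
- Grade 3–4 neutropenia 46% and grade 3–4 diarrhea about 18% (Background), used as the non-PM rates.
- PM share: not given in the article. Assumed 10% of 84, so 8 PMs and 76 non-PMs; range 5–15%, so 4 to 13 PMs.
- Dose-toxicity relation: not given. Two assumed cases: flat between 70% and 100%, or proportional to dose.
- Meaning of similar: taken first as no significant difference, two-sided Fisher test at 5%. This is also an assumption.

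**Step 1: what the comparison identifies.** Let g be the PM/non-PM risk ratio at equal dose and d the ratio of toxicity at 70% to that at 100% dose. In a simple multiplicative model the observed ratio is R = g × d. If R = 1, then g = 1/d.
- Flat toxicity (d = 1): g = 1, no genotype effect.
- Proportional toxicity (d = 0.7): g = 1/0.7 = 1.43, a clear genotype effect.

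The same result supports opposite conclusions depending on d, which the study does not estimate.

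**Step 2: what an irrelevant genotype predicts (g = 1).** With flat toxicity the rates are 46% and 46%. With proportional toxicity PMs have 0.7 × 46% = 32.2% against 46%, a gap of 13.8 points. For diarrhea it is 0.7 × 18% = 12.6% against 18%, a gap of 5.4 points. In the proportional case PMs do better than non-PMs; the rates are not truly similar.

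**Step 3: can the study see the difference?** The probability of no significant difference is the sum of Binomial(n_PM, p_PM) × Binomial(n_non, 0.46) over all tables with Fisher p > 0.05.

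| True PM neutropenia rate | 4 vs 80 | 8 vs 76 | 13 vs 71 |
|---|---|---|---|
| 32.2% (genotype irrelevant, proportional) | 0.981 | 0.944 | 0.899 |
| 46% (exact offset, or genotype irrelevant and flat) | 0.973 | 0.977 | 0.969 |
| 69% (reduction insufficient, ratio 1.5) | 0.892 | 0.856 | 0.736 |

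At 8 vs 76 and a true PM rate of 65% the probability is 0.898. For diarrhea at 8 vs 76 it is 0.993 (12.6%), 0.976 (18%) and 0.909 (27%).

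The evidence in a non-significant result at 8 vs 76 is the ratio of these probabilities. For exact offset against an irrelevant genotype it is 0.977/0.944 = 1.03 (proportional) or 1.00 (flat). Against PMs at 65% it is 0.977/0.898 = 1.09.

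**Step 4: another reading of similar.** If it means PMs at most 15 points worse, the probabilities at 8 vs 76 are 0.78 (46%), 0.94 (32.2%) and 0.39 (65%). This reading does react to an insufficient reduction, but an irrelevant genotype passes at least as often as a relevant one that is offset.

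**Step 5: precision.** The 95% half-width for the PM minus non-PM difference at 46% is 1.96 × √[0.46 × 0.54 × (1/8 + 1/76)] = 36 points, against the 13.8-point gap. At 18% it is 28 points, against 5.4. Separating 32.2% from 46% with 80% power at a 1:9 split needs about 110 PMs, more than the 104 patients to be enrolled in all; for diarrhea it needs about 403.

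**Step 6: the contrast within the study at equal starting dose.** IMs and NMs both keep the unreduced starting dose. With an assumed 36 IMs and 40 NMs, the half-width is 1.96 × √[0.46 × 0.54 × (1/36 + 1/40)] = 22 points.

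**The case against.** A reader might infer that the two states, irrelevant genotype and offset genotype effect, give the same data at any sample size, so that an irrelevant biomarker would simply be reported as validated. The article does not support that. If toxicity falls with dose, an irrelevant genotype predicts fewer events in PMs, and true similarity would then count in favour of a genotype effect. With 400 PMs, 3,600 non-PMs and similarity defined as within ±10 points, the criterion is met with probability 1.00 at equal rates and 0.06 at 32.2% versus 46%. A margin wider than the 13.8-point gap would not separate them as well. How far the criterion discriminates thus depends on margin, size and the dose-toxicity relation.

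Three further points are fair.

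- The historical full-dose PM comparison partly supplies the missing contrast. Historical PMs at full dose against the study's full-dose non-PMs is a same-dose genotype contrast, though not concurrent.
- The stated objective is safety, the neutropenia association is taken as already shown, and the sentence claims further support, not proof.
- IM versus NM does not test the PM versus non-PM split on which dosing acts.

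These points remove any claim that the design can never tell. They do not rescue the sentence. It draws on the internal comparison alone, relies on a dose-toxicity relation that is not stated, and would be applied to a group in which non-difference is expected under nearly every scenario.

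**Conclusion.** The point holds in a limited form. Genotype and starting dose are confounded by design, so similar severe toxicity in PMs and non-PMs cannot by itself isolate a genotype effect. An irrelevant genotype gives truly similar rates only if toxicity is roughly flat between 70% and 100% dose, or if later dose changes even the groups out. At the group sizes likely here, no significant difference in neutropenia is expected about 90–98% of the time whether genotype is irrelevant, exactly offset, or the reduction is insufficient (PMs at 65%). Such a result carries almost no evidence on validity.

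The figures rest on 8 PMs among 84, a non-PM rate of 46%, and reading similar as non-significant. With 13 PMs and a PM rate of 69% the probability falls to 0.736, so a gross excess in PMs would be detected somewhat more often. The confounding itself depends on none of these assumptions. This should be changed, but it concerns an inference and one added analysis; it does not undermine the tolerability comparison.

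**What to change.** 1. **Discussion.** Limit the conclusion from the PM versus non-PM comparison to tolerability of the genotype-guided strategy. Report it as a risk difference with 95% CI, not as absence of a significant difference.
2. **Discussion.** Rest any statement on biomarker validity on the comparison with historical full-dose PMs that is already planned.
3. **Analysis of main outcome parameters.** Add, as support, IM versus NM at the same starting dose: severe neutropenia and severe diarrhea, risk difference with 95% CI, adjusted for regimen. Keep the pooled non-PM group for the tolerability comparison.

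Cost: one reworded passage and one analysis on data already collected. The claim becomes narrower. The historical comparison is not concurrent. The IM versus NM contrast is observational and imprecise (about ±22 points under the assumed 36 and 40 patients), and a null result there would not rule out an effect in homozygotes. No dose or clinical rule changes.
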